The prevalence of paratonia ranges from 5% in the early stages of dementia to 100% in the advanced stages [2,5]. We found an estimated prevalence of paratonia of approximately 80% in a group of Dutch nursing home patients with dementia [6]. Passive movement therapy (PMT) is a therapeutic intervention designed to increase the passive extensibility of muscles, ligaments and collagen in order to achieve maximal joint range of motion [7,8]. A recent NIVEL report revealed that PMT is with 28.2% one of the main physiotherapeutic interventions in Dutch nursing homes, with an average duration of 30 minutes per patient per week [9]. This therapy is generally believed to be effective in patients with paratonia [10,11]. Professional workers claim that this therapy, if given shortly before washing and bathing, facilitates the care for the patients, due to improved range of motion of affected limbs. Investigations in other populations, e.g., patients with spasticity and contractures show a temporal effect or a so-called elastic deformation due to the visco-elastic properties in all tissues [7]. However, after 20 to 30 minutes, joint range of motion returns to the starting values. Plastic deformation, or a permanent effect, is only possible if the patient can actively use the gained mobility[7,8]. Furthermore, animal studies indicate that when activated muscles fibres are stretched, which is the case with PMT in paratonia, older tissues are more susceptible to injury on sarcomere level [12]. Given the fact that these frail patients, who often show signs of discomfort during the treatment, are prone to injury and are not able to actively use regained mobility PMT is controversial. Nonetheless, maybe because of a lack of alternatives, or because of pressure of concerned relatives, physicians and physiotherapist start PMT. A pilot study in 15 patients with paratonia confirmed that PMT had positive short term effects, but trend analyses of long term effects showed that after 3 weeks hypertonia increased slightly in 30% in the PMT group in comparison with 10% in the control groups, indicating a possible association with muscle fibre injuries [3]. We feel this is a relevant finding, however, the small sample size of this pilot study, and the lack of a clear operational definition of paratonia did not allow for firm conclusions concerning the efficacy of PMT.

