### Sample size

The Modified Ashworth Scale is our primary outcome measure. A trend analysis of the pilot study data showed a worsening of paratonia in 30% of the group with PMT and in 10%, possibly due to natural course, of the group with usual care without PMT [3]. We consider this effect as clinical important. With an alpha of 0.05 and a power of 80% a sample size of 69 patients per group (taking into account a drop-out percentage of 10%) is needed to detect this effect.

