### Analysis

All data will be analysed with SPSS 15.0. The Modified Ashworth scale, an ordinal 5-point scale, will be measured at 3 times, at baseline (T0) after 2 weeks (T1) and after 4 weeks (T2). Our premise in this study is that PMT causes an accelerated worsening of paratonia over 4 weeks time. Success of the intervention is defined as a significant (p < 0.05) difference between the proportion of change on the modified Ashworth scale in the two groups.

To determine any development or change over time of The Modified Ashworth score in the two groups the Stuart-Maxwell statistic will be used.

The difference in proportion of change between the two groups will be calculated and tested for significance [20]. However controlling for relevant confounders e.g. age, sex, severity and type of dementia is not possible with this analysis. Therefore a multiple logistic regression analysis will be performed on the dichotomised outcome measure, "declined" and "stable/improved", of the difference on T0 and T2 on The Modified Ashworth score.

Missing data will be assumed to be missing at random. The Last Observation Carried Forward method will be used in those cases with no last measurement (T2) yet with valid data from the second assessment (T1). Analyses will be carried out according to the intention to treat principle.

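### Carrying the week-2 Ashworth score forward to week 4 does not follow from the stated missing-at-random assumption and, if decline continues after week 2, can understate harm from passive movement therapy

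*Protocol article*

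**What the plan says.** The protocol article, Analysis section, measures the Modified Ashworth score at baseline (T0), week 2 (T1) and week 4 (T2). The logistic regression uses a two-way outcome, declined or not, formed from the T0 to T2 difference. On missing data it says "Missing data will be assumed to be missing at random". The next sentence reads "The Last Observation Carried Forward method will be used in those cases with no last measurement (T2"), on condition that a usable T1 score exists. It then adds "Analyses will be carried out according to the intention to treat principle".

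On the expected course, the same section states "Our premise in this study is that PMT causes an accelerated worsening of paratonia over 4 weeks time". The Background section reports the pilot result: "after 3 weeks hypertonia increased slightly in 30% in the PMT group in comparison with 10% in the control groups". The Sample size section uses those two rates to arrive at 69 patients per group, allowing for 10% dropout with no split by arm.

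**The concern.** Missing at random describes why values are missing: given the observed data, missingness does not depend on the unseen value. Last observation carried forward (LOCF) instead fixes what the unseen value is, namely the T1 score. The first statement does not justify the second.

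The implied flat course after week 2 is also awkward here. The trial looks for worsening over four weeks, and its effect size comes from a pilot observation at three weeks, after T1. A dropout who would first have declined between T1 and T2 is scored as not declined.

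Two statements make higher dropout under PMT plausible, though neither gives a number. The Background section notes frequent signs of discomfort during treatment. The Patients section removes participants who show in any way that they do not approve of taking part. In the control arm the therapist only stays in the room. If exits concentrate in the PMT arm, LOCF hides more would-be decliners there, and the trial could miss the harm it is sized to detect.

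**Working it through.** **Plan's own figure.** Inputs from the Sample size section: 30% v 10%, alpha 0.05 (taken as two-sided), power 80%, dropout 10%. With mean proportion 0.20:

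n = [1.960 × √(2 × 0.20 × 0.80) + 0.842 × √(0.30 × 0.70 + 0.10 × 0.90)]² / 0.20² = 61.6, so 62 per group. Then 62 / 0.90 = 68.9, so 69. The stated figure reproduces, and the sample size is not in question.

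**Effect of LOCF.** Let p be the true T2 decline rate in an arm, d its dropout between T1 and T2, and f the share of T2 decliners who have already declined at T1. The documents give no T1 rates, so f is an assumption, taken as equal in both arms. With dropout unrelated to outcome within arm:

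rate under LOCF = (1 − d) × p + d × f × p = p × [1 − d × (1 − f)]

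loss in the difference, in percentage points = (1 − f) × (30 × d_PMT − 10 × d_control)

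For f below 1, the difference shrinks whenever d_PMT exceeds one third of d_control. This includes equal dropout.

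**Comparator.** Observed T2 data give an unbiased difference of 20 points under the same dropout, with fewer patients: 69 × 0.90 = 62 per arm at 10%, or 69 × 0.80 = 55 v 69 × 0.95 = 66 at 20% v 5%. Power throughout is the exact power of the uncorrected chi-square test; LOCF keeps 69 per arm.

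| Dropout PMT v control | f | LOCF rates | Difference (points) | Power, LOCF | Power, observed T2 |
|---|---|---|---|---|---|
| 10% v 10% (planned) | 0.5 | 28.5% v 9.5% | 19.0 | 0.83 | 0.81 |
| 10% v 10% (planned) | 0 | 27.0% v 9.0% | 18.0 | 0.81 | 0.81 |
| 20% v 5% (assumed) | 0.5 | 27.0% v 9.75% | 17.3 | 0.76 | 0.80 |
| 20% v 5% (assumed) | 0 | 24.0% v 9.5% | 14.5 | 0.64 | 0.80 |

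With f = 1 (all decline present by T1) the difference stays at 20 points in every row.

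**Timing of dropout.** If half of the 20% v 5% dropout comes before T1, where the LOCF rule does not apply, the remaining dropout among those with T1 is 0.10/0.90 = 11.1% v 0.025/0.975 = 2.6%. The difference is then 18.5 points (f = 0.5) or 16.9 points (f = 0).

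**Informative dropout.** Suppose 60% of PMT dropouts would decline, with 20% v 5% dropout and 30% declining in the PMT arm overall. LOCF gives 8.5 points (f = 0), 14.3 (f = 0.5) or 20 (f = 1). Among observed PMT patients the rate is (0.30 − 0.20 × 0.60) / 0.80 = 22.5%, so observed T2 data give 12.5 points. Neither method is reliable here.

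**The case against.** The best defence is that little is lost under the plan's own assumptions. At 10% dropout per arm the difference shrinks by 2 points at most, and LOCF has as much power as observed T2 data, because it keeps more patients. That stands. The 20% v 5% split is not in the documents, and the worst figures need every dropout to come after T1.

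The premise can also be read as worsening faster than the natural course, not as a rate that rises after week 2. That is a fair reading. It still leaves no reason to expect a flat score between T1 and T2.

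A reader might infer more than the documents support:

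- **That LOCF always shrinks the effect.** It does not if decline is complete by T1. With 5% PMT v 15% control dropout, 30 × 0.05 − 10 × 0.15 = 0, so nothing is lost. With informative PMT dropout, LOCF can lie closer to the truth than observed data.
- **That LOCF takes power from 0.86 to 0.76.** The 0.86 is for 69 per arm with no dropout at all. It charges LOCF for a loss that any method would suffer; the fair comparator at 20% v 5% is 0.80.
- **That patients without T1 are dropped, in breach of intention to treat.** The article does not say how they are handled, and an article may leave this to the full protocol or analysis plan.
- **That the standard errors are materially wrong.** Single imputation does treat filled-in values as observed, but nothing in the documents lets one size the effect.

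**Conclusion.** The mismatch is certain: the plan states one missing-data assumption and prescribes a method that needs a different and stronger one, which its own premise and pilot timing make doubtful. Bias toward no difference, and so toward missing harm, is conditional. It needs some decline after week 2 and PMT dropout that is not clearly lower than in controls. Both are plausible from the documents; neither is established.

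The size is small at the planned dropout and becomes material only with unequal dropout, as in the 20% v 5% rows, which rest on assumed dropout and assumed T1 rates. This is a point that should be fixed. It is not a flaw that invalidates the design.

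**What to change.** Keep the planned outcome (declined v stable or improved, T0 to T2), so that the quantity estimated is unchanged. Replace LOCF in the main analysis with multiple imputation of T2, done by arm, from T0, T1 where available, nursing home and dementia severity, including all randomised patients. This agrees with the stated missing-at-random assumption. Keep LOCF as a sensitivity analysis only.

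Add a sensitivity analysis that varies the assumed decline rate among dropouts separately in each arm, such as a delta or tipping-point analysis. Do not simply count every missing T2 as worsened. With no true effect (10% in both arms) and 20% v 5% dropout, that rule gives 0.80 × 10% + 20% = 28% v 0.95 × 10% + 5% = 14.5%, and a significant result about 50% of the time at 69 per arm.

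The cost is a change of wording and some extra programming, possibly outside SPSS 15.0. The variables needed are already collected. The change should be settled before unblinding.

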Before designing a new trial with sufficient power we therefore initiated a Delphi procedure with known experts in the field to achieve a new consensus definition of paratonia. After four Delphi-rounds, the experts agreed on 7 criteria for operational defining paratonia (see below) [13]. Consequently these criteria have been assessed on validity and reliability in a 3-phase cross-sectional study in which this definition was tailored even further and in which we developed an assessment instrument (the Paratonia Assessment Instrument, PAI) for an instant diagnosis of paratonia, thus providing researchers an operational tool for future trials on paratonia [6].

*"Paratonia is a form of hypertonia with an involuntary variable resistance during passive movement. The nature of paratonia may change with progression of the dementing illness (e.g. active assistance (Mitgehen) is more common early in the course of degenerative dementias, whilst active resistance is more common later in the course of the disease). The degree of resistance varies depending on the speed of movement (e.g. a low resistance to slow movement and a high resistance to fast movement). Paratonia increases with progression of dementia. Furthermore, the resistance to passive movement is in any direction and there is no clasp-knife phenomenon." The resistance must be felt in either two directions in one limb or in two different limbs*.

We designed a randomized clinical trial in order to answer three research questions; first, is passive movement therapy an effective intervention on the severity of paratonia in comparison with usual care without passive movement therapy?

Second, is passive movement therapy an effective intervention for improvement of daily care? And finally, does PMT reduce pain during daily care in patients with moderate to severe paratonia.

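### The plan assumes data missing at random but carries T1 forward to a missing T2, which that assumption does not justify and which would probably attenuate the difference in worsening

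*Protocol article*

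**What the plan says.** The primary outcome is the Modified Ashworth score at baseline (T0), after 2 weeks (T1) and after 4 weeks (T2). The Analysis section compares the two arms on the proportion that changed. It adds a logistic regression on a two-way outcome, declined or not, taken from the T0 to T2 difference.

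On missing values the same section makes two consecutive statements. The first is "Missing data will be assumed to be missing at random". The second is "The Last Observation Carried Forward method will be used in those cases with no last measurement (T2) yet with valid data"; the value carried is the T1 score.

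The section also gives the expected course: "Our premise in this study is that PMT causes an accelerated worsening of paratonia over 4 weeks time". The Background places the pilot's difference between the arms after 3 weeks. The Sample size section builds on that pilot, which "showed a worsening of paratonia in 30% of the group with PMT and in 10%, possibly due to natural course" of controls, and reaches its total "taking into account a drop-out percentage of 10" per cent.

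**The concern.** Missing at random means that, given what was observed (arm, T0, T1), the unseen T2 scores of lost patients follow the same distribution as those of comparable patients who stayed. Carry-forward does not use that distribution. It sets T2 equal to T1, which is a separate and stronger assumption of no change from week 2 to week 4.

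The plan gives reasons to doubt that assumption in both arms. The PMT arm is expected to go on worsening up to week 4, and the 10% worsening in controls is put down to a possible natural course. The pilot signal was seen a week later than T1. A patient lost after T1 who would have worsened only in weeks 3 or 4 is coded as stable or improved in both planned analyses. The filled value then counts as a real measurement, so the standard error is too small.

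The hypothesis is harm and the results are meant for a practice guideline, so a bias towards no difference matters.

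**Working it through.** **Inputs from the protocol.** Worsening of 30% (PMT) and 10% (control), alpha 0.05, power 80%, 69 per group and 10% drop-out (Sample size); T1 at 2 weeks and T2 at 4 weeks (Analysis).

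**Assumptions, because the protocol gives no figure.** The test is two-sided. Every lost patient has a T1. Loss is unrelated to outcome within arm, a special case of missing at random. Worsening seen at T1 persists to T2. A share f of the T2 worsening is already present at T1, tried at 0, 0.25 and 0.5. The split of loss by arm is varied.

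**The plan's own figure.** For two proportions, n = [1.96·√(2·0.2·0.8) + 0.842·√(0.3·0.7 + 0.1·0.9)]² / 0.2² = 61.6, so 62 per group. Then 62/0.9 = 68.9, so 69. The stated size is reproduced.

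**Formula.** With true T2 worsening p and a share d lost after T1, the expected proportion declined under carry-forward is p(1 − d) + f·p·d. Power below is exact for the Pearson chi-squared test (sum over all binomial outcomes), with 69 per arm under carry-forward.

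| Loss PMT / control | f | PMT | Control | Difference (points) | Power |
|---|---|---|---|---|---|
| 10% / 10% | 0 | 27.0% | 9.0% | 18.0 | 80.7% |
| 10% / 10% | 0.25 | 27.75% | 9.25% | 18.5 | 82.1% |
| 10% / 10% | 0.5 | 28.5% | 9.5% | 19.0 | 83.3% |
| 20% / 5% | 0.25 | 25.5% | 9.6% | 15.9 | 70.5% |
| 20% / 5% | 0.5 | 27.0% | 9.75% | 17.3 | 76.3% |
| 0% / 20% | 0.5 | 30.0% | 9.0% | 21.0 | – |

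Example, row 5: PMT 0.30·0.80 + 0.5·0.30·0.20 = 0.27; control 0.10·0.95 + 0.5·0.10·0.05 = 0.0975.

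**Comparator.** The fair baseline is the power left after the same loss. With 62 completers per arm (69·0.9) it is 81.0%. With 55 v 66 completers (69·0.80 and 69·0.95, rounded) it is 80.0%.

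**Is dropping the incomplete patients enough?** Take the PMT arm with 15% worsened at T1, of whom 90% are still worse at T2. To reach 30% at T2, the rate among those not worse at T1 must be (0.30 − 0.135)/0.85 = 0.194. Let 30% of the T1-worsened be lost and 10% overall, so loss among the others is (0.10 − 0.045)/0.85 = 0.065. This is missing at random given T1.
- Carry-forward: 0.15·(0.7·0.9 + 0.3) + 0.85·0.935·0.194 = 29.4%.
- Completers only: (0.15·0.7·0.9 + 0.85·0.935·0.194)/0.90 = 27.6%.

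Both miss the true 30%. The method has to use T1 to predict T2.

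**The case against.** The strongest reply is that little is lost at the drop-out the trial planned for. With 10% lost in each arm, the bias is 1 to 2 points and power stays at or slightly above that of the completers. This stands: at planned drop-out the fault is a biased estimate and overstated certainty, not a loss of power.

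The direction is not fixed either. Heavier loss in control gives 21 points instead of 20 in the last row of the table. Paratonia is defined by variable resistance, and the intrarater agreement quoted for the scale (Kendall's Tb 0.62–0.80) is moderate, so some T1 worsening may revert; carry-forward would then count a non-decliner as declined. This stands too.

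Heavier loss under PMT is an inference. The Background reports frequent signs of discomfort during treatment, and the Patients section removes anyone who objects, verbally or not, so it is plausible. But one drop-out figure is given with no split by arm, and patients who object early may leave before T1, where carry-forward does not apply. The 20%/5% rows are illustrations.

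Three stronger readings are tempting and not supported:
- A reader might infer that the rule hides the harm. The figures show attenuation, and only under stated conditions.
- A reader might set the carry-forward powers against 86%, the exact power of 69 per arm. That assumes nobody is lost, and no analysis recovers it once patients leave.
- A reader might suppose that the patients lost are exactly those who worsen later. Loss would then depend on the unseen T2, which is outside missing at random. If the lost 10% of the PMT arm all worsened after T1, imputation from T0 and T1 would give about 20/90 = 22.2%, against 20% by carry-forward and a true 30%. Most of that error cannot be charged to carry-forward.

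Finally, "Paratonia increases with progression of dementia" describes the course of the disease. It is weak evidence about change between weeks 2 and 4; the premise and the pilot timing carry the argument.

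**Conclusion.** The concern holds as a mismatch between a stated assumption and a stated method on the primary outcome. Both are fixed in the article, so this is not a detail left to an unseen analysis plan.

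With equal loss, or heavier loss under PMT, carry-forward attenuates the difference in the declined proportion, provided T1 worsening persists. The size is 1 to 2 points out of 20 at 10% loss in each arm (f from 0 to 0.5). It is about 3 to 4 points at 20% v 5% loss (f of 0.5 or 0.25), where power is 76% or 71% against about 80% for the completers. If loss is heavier in control, a slight exaggeration is possible. All sizes depend on f and on the split of loss, which the protocol does not give. The change should be made, because the present rule contradicts the trial's own premise and a consistent one costs little.

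**What to change.** In the Analysis section, replace carry-forward as the primary method by one that is valid under missing at random and uses T0 and T1. Two options:
- Multiple imputation of the T2 outcome from arm, T0, T1 and a small set of baseline covariates. The model must stay small: about 6 control declines are expected among 62 completers (0.10·62).
- A longitudinal model of the T1 and T2 outcomes.

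Then run the planned comparison of declined against stable or improved.

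Keep carry-forward as a sensitivity analysis. Add one that varies the assumption about missing T2 values in both arms. Counting only missing PMT values as worsened would lean towards the team's own hypothesis.

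The cost is a few sentences, some analyst time, possibly software other than SPSS 15.0, and a slightly wider confidence interval. No new data are needed.

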### Study timeline

The estimated project time is 18 months. The project will start with an extensive training of relevant staff of all participating nursing homes. The training period will take two months. After this training the inclusion period will start and will run for twelve months. Analysis of data and writing of the report is estimated to take 4 months.

The study has been approved by the local ethical committee CMO nr. 2006/1567, ABR file nr. NL13777.091.06.

The investigator will notify the accredited local ethical committee of the end of the study within a period of 8 weeks. The end of the study is defined as the last patient's last follow-up measurement. Within one year after the end of the study the investigator will submit a final study report with the results, including any publication/abstracts of the study to the accredited local ethical committee. The investigators are not restricted in any way to publish the results of the study.

## Discussion

This study is the first RCT of this size to gain further insight on the effect of passive movement therapy on the severity of paratonia.

### Ethical aspects

PMT is a very common physiotherapeutic intervention in patients with moderate to severe paratonia. Although it is controversial and possibly harmful for these frail elderly, in lack of evidence based alternative interventions, most therapists perform PMT. For this reason we designed this RCT in a very pragmatic way, close to daily practice bounded by ethical aspects limiting the time frame of 4 weeks per participant and using assessment tools that are valid and reliable but above all with a minimal burden for the frail participants. Although we realise that further assessments after the end of the treatment period could have given more insight in the duration of the effect of PMT, the frailty of the participants prevails over the aims of research. For the same reason we decided to use no invasive methods, such as muscle biopsy to assess possible tissue damage.

